### 2.5 Intervention

#### 2.5.1 Composition, preparation, and administration of the trial medication

The treatment group received Yiqi Gubiao Pill (specific composition detailed in Table 1; each pill containing 0.19 g, prepared by the Department of TCM Preparation, Affiliated Hospital of Traditional Chinese Medicine, Xinjiang Medical University). Administration consisted of 10 pills orally three times daily after meals, continued for 12 weeks. The control group received a placebo matching Yiqi Gubiao Pill in appearance and core color (primary ingredients: starch and caramel; prepared by the TCM Preparation Room, Affiliated Traditional Chinese Medicine Hospital of Xinjiang Medical University). Participants were instructed to take 10 placebo pills orally three times daily after meals for 12 weeks (Figure 2).

**TABLE 1 T1:** The composition of Yiqi Gubiao Pill.

Chinese name	Latin name	Medicinal site
Dang-shen	Codonopsis radix	Root
Fu-xiao-mai	*Triticum aestivum*	Fruit
Bai-zhu	Atractylodes macrocephala Koidz	Rhizome
Ban-xia	Pinelliae rhizoma	Tuber
Chen-pi	Citri reticulatae pericarpium	Pericarp
Zi-su-zi	Perillae fructus	Fruit
Fu-ling	Poria cocos	Sclerotium
Yi-yi-ren	Coicis semen	Fruit
Fang-feng	Saposhnikoviae radix	Root
Kuan-dong-hua	Farfarae flos	Flower bud
Bei-mu	Fritillariae pallidiflorae bulbus	Bulblet
Huang-qin	Scutellariae radix	Root
Pi-pa-ye	Eriobotryae folium	Leafage

**FIGURE 2 F2:**
[figure not shown]
Yiqi Gubiao Pill and Control drug. **(A)** Appearance and Packaging of Yiqi Gubiao Pill; **(B)** Comparison of Yiqi Gubiao Pill and Placebo in Appearance.

#### 2.5.2 Conventional treatment

Both treatment and control groups receive standardized anti-tuberculosis therapy following the WHO-recommended RIPE regimen—an intensive 8-week phase with daily rifampicin, isoniazid, pyrazinamide, and ethambutol, followed by a 16-week continuation phase with rifampicin and isoniazid—and concurrently receive guideline-concordant COPD management, including maintenance bronchodilator therapy.

### 2.6 Outcome

#### 2.6.1 Primary outcome

Lung function, long-term lung function decline and quality of life were established as primary efficacy endpoints.

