##### 2.6.1.1 Lung function assessment​​

Pulmonary function testing (PFT) will be conducted under standardized protocols to ensure data validity and reproducibility. Patients will be instructed to abstain from inhaled bronchodilators for at least 24 h prior to testing to avoid transient airway dilation effects. Resting heart rate will be maintained below 120 bpm to minimize cardiovascular interference during spirometry. Key spirometric parameters included:① Forced Vital Capacity (FVC)​​: Measures the total volume of air exhaled forcefully after maximal inhalation. Reduced FVC indicates severe obstructive conditions.② FVC%​​: The ratio of measured FVC to predicted values (based on age, sex, and height). Values < 80% suggest significant impairment.③ FEV1%​​: The percentage of predicted forced expiratory volume in the first second, reflecting airflow limitation severity. Classified as mild (≥80%), moderate (50%–79%), or severe (<50%).④ FEV1/FVC Ratio​​: Critical for distinguishing obstructive (ratio <0.7) and restrictive (ratio ≥0.7 with reduced FVC) disorders.

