##### 2.6.1.2 Long-term lung function decline

Long-term decline in lung function will be evaluated through serial spirometry conducted at baseline and predefined follow-up intervals (every 3 months). Patients with at least three valid pulmonary function tests over a 12- month period will be included in the analysis of decline trajectory. The following parameters will be used to quantify and classify lung function deterioration:① Annual FEV_1_ Decline (mL/year): The change in forced expiratory volume in 1 s (FEV_1_) over time will be calculated and expressed per year. A decline greater than 60 mL/year will be defined as “rapid decline,” in alignment with thresholds reported in GOLD and SPIROMICS cohorts. Declines between 30 and 60 mL/year will be considered moderate, while declines under 30 mL/year will reflect physiological aging.② Annual Change in FEV_1_% Predicted: The annual reduction in FEV_1_ as a percentage of predicted values will be computed. A reduction exceeding 5% per year will indicate clinically significant progression.③ FVC and FVC% Predicted Trends: Longitudinal changes in forced vital capacity (FVC) and its percentage of predicted will be monitored to detect potential restrictive patterns or lung volume loss.④ FEV_1_/FVC Ratio Decline: The ratio of FEV_1_ to FVC will be tracked over time. A progressive decrease in this ratio will reflect worsening airflow obstruction, particularly relevant in COPD progression.

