##### 2.6.1.3 ​​Quality of life (QL) evaluation​​

QL was assessed using validated tools:① COPD Assessment Test (CAT)​​: An eight-item questionnaire scoring symptoms (cough, dyspnea) and functional limitations (0–40 scale). A 5-point change indicates clinically meaningful improvement.② mMRC Dyspnea Scale​​: Grades breathlessness from 0 (no dyspnea) to 4 (dyspnea at rest). Scores ≥2 correlate with increased hospitalization risk.③ Baseline Dyspnea Index (BDI)​​ and ​​Transition Dyspnea Index (TDI)​​: BDI assesses dyspnea impact on daily activities (e.g., task difficulty), while TDI measures changes post-treatment. A TDI score ≥1 signifies meaningful improvement.​​④ Chest Radiography​​: Screened for structural abnormalities (e.g., hyperinflation, effusions) but limited in detecting early small airway disease.​​⑤ High-Resolution CT (HRCT)​​: Quantified emphysema extent, airway wall thickness, and fibrosis patterns. Dynamic CT evaluated ventilation-perfusion mismatches in advanced cases.⑥ Acute Exacerbation of COPD (AECOPD): Exacerbation Frequency Classification: Based on events in the previous 12 months. Infrequent exacerbators: ≤1 exacerbation/year without hospitalization; Frequent exacerbators: ≥2 exacerbations/year or ≥1 requiring hospitalization.

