### 2.7 Data collection and management

Data collection will be carried out before, during, and after treatment (Table 2). Data will be recorded on pre-designed case report forms (CRF) and transferred to an electronic format (RevMan 5.3) for storage and data backup. All patient identity information will be encoded.

**TABLE 2 T2:** Participant enrollment process, interventions, and outcome measures.

Items	Baseline	Treatment phase (monitor monthly)			Follow-up phase (monitor monthly)		
		1 month	2 months	3 months	3 months	6 months	12 months
Enrolment							
Recruitment	●						
Eligibility Screening	●						
Signed written informed consent	●						
Allocation	●						
Intervention							
Yiqi Gubiao pill (Treatment group)		●	●	●	●	●	●
Yiqi Gubiao pill Placebo (Control Group)		●	●	●	●	●	●
Outcomes							
forced vital capacity (FVC)	●	●	●	●	●	●	●
the percentage of FVC predicted (FVC%)	●	●	●	●	●	●	●
the percentage of forced expiratory volume in one second predicted (FEV1%)	●	●	●	●	●	●	●
FEV1/FVC	●	●	●	●	●	●	●
CAT score	●	●	●	●	●	●	●
mMRC score	●	●	●	●	●	●	●
BDI score	●	●	●	●	●	●	●
TDI score	●	●	●	●	●	●	●
chest X-ray/CT	●	●	●	●	●	●	●
Traditional Chinese Medicine Symptom (TCMS) score	●	●	●	●	●	●	●
Security							
All adverse events (including symptoms, signs, etc.)		●	●	●	●	●	●
Liver function: alanine aminotransferase, aspartate aminotransferase, total bilirubin, albumin, globulin	●	●	●	●	●	●	●
Renal function: uric acid, urea nitrogen, serum creatinine, β2-microglobulin, urinary protein, carbon dioxide binding rate, cystatin C	●	●	●	●	●	●	●

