### 2.8 Data analysis

Two researchers independently entered observational data to establish a standardized database, with subsequent statistical analyses performed using SPSS 25.0. Quantitative variables exhibiting normal or approximately normal distributions are expressed as mean ± standard deviation (x̄±s). Between-group comparisons of means were analyzed via independent t-tests, while within-group longitudinal changes were assessed using paired t-tests. Categorical data were evaluated through χ^2^ tests or Wilcoxon rank-sum tests, and ordinal data were analyzed using non-parametric methods (e.g., Kruskal-Wallis test for multi-group comparisons). All statistical inferences employed two-tailed tests with a predefined significance threshold of α = 0.05.

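### Three primary domains holding 14 measures, with no primary variable or time point and every test at 0.05, leave the primary error rate above 5% if any one significant result counts as success.

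*Protocol article*

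**What the plan says.** The protocol article, section 2.6.1, sets the primary outcome: "Lung function, long-term lung function decline and quality of life were established as primary efficacy endpoints". Each domain is then filled by a numbered list.

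- Section 2.6.1.1 ("Key spirometric parameters included") has four items: FVC, FVC% predicted, FEV1% predicted and FEV1/FVC.
- Section 2.6.1.2 ("The following parameters will be used to quantify and classify lung function deterioration") has four: annual FEV1 decline, annual change in FEV1% predicted, FVC and FVC% trends, and decline in FEV1/FVC.
- Section 2.6.1.3 ("QL was assessed using validated tools") has six: CAT, mMRC, BDI/TDI, chest radiography, HRCT and acute exacerbations of COPD. The last is defined by "Exacerbation Frequency Classification: Based on events in the previous 12 months".

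Table 2 in section 2.7 has three post-baseline columns under "Treatment phase (monitor monthly" and three under "Follow-up phase (monitor monthly". None is singled out as the primary time, and there is no exacerbation row.

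Section 2.8 sets the error rule: "All statistical inferences employed two-tailed tests with a predefined significance threshold of α = 0.05". It gives no hierarchy, co-primary rule or adjustment.

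Section 2.4 gives a minimum of 31 per group, taken from a previous randomised trial. It does not state the endpoint, effect size, standard deviation or power.

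**The concern.** A confirmatory trial needs to say in advance which result decides it. Here three domains have equal primary status, each contains several measures, and the level is 0.05 throughout. A reader of the final report could not tell a planned success from the most favourable of several chances. If any one significant measure may be reported as a positive primary outcome, the 5% level no longer describes the risk of a false claim.

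Two features make the quality-of-life domain a weak primary in its own right. Radiography and HRCT do not measure quality of life. The exacerbation class looks back over 12 months without tying that window to randomisation, so it can count events that treatment could not have influenced.

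**Working it through.** **1. Size of the family.** Numbered items: 4 + 4 + 6 = 14. Not all can be tested at one visit. The four decline items are annualised changes or trends over serial spirometry, and exacerbations are not scheduled in Table 2. That leaves 14 − 4 − 1 = 9 items at a single visit, or 8 if radiography and HRCT are taken together, as in Table 2's single chest X-ray/CT row.

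**2. Chance of at least one false positive.** Assume no true effect on any measure, each test at two-sided 0.05, and success if any test is significant. For k independent tests the chance is 1 − 0.95^k. For correlated tests I used equicorrelated normal test statistics. The correlations are assumptions, since the article gives none.

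| Family | k | Independent | r = 0.3 | r = 0.5 | r = 0.7 | r = 0.9 |
|---|---|---|---|---|---|---|
| One test per domain | 3 | 14.3% | 13.6% | 12.5% | 10.9% | 8.4% |
| Items at one visit, imaging as one | 8 | 33.7% | 30.0% | 25.0% | 19.1% | 11.9% |
| Items at one visit, imaging as two | 9 | 37.0% | 32.6% | 26.9% | 20.2% | 12.4% |
| All measures, tested once each | 14 | 51.2% | 43.8% | 34.8% | 24.9% | 14.1% |

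For example, 1 − 0.95^3 = 1 − 0.857 = 0.143. Every cell is above 5%.

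**3. Power if three primaries are kept and adjusted.** The 31 per group cannot be reproduced, because section 2.4 gives no inputs. Bonferroni over three domains tests each at 0.05/3 = 0.0167. Two assumptions about how 31 was reached, using the two-sample t-test:

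- Sized for 80% power at 0.05: standardised difference 0.72. Power at 0.0167 with 31 per group is 65%.
- Sized for 90% power at 0.05: standardised difference 0.84. Power at 0.0167 with 31 per group is 79%.

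The normal approximation gives 66% and 80%.

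**4. Exacerbation window.** At an assessment m months after randomisation, with m below 12, the share of the look-back that precedes randomisation is (12 − m)/12.

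- m = 3 (end of treatment): 9/12 = 75%.
- m = 6: 6/12 = 50%.
- m = 9: 3/12 = 25%.
- m = 12 or later: 0%.

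Table 2 shows a 3-month column in both phases and does not say whether follow-up months run from randomisation or from the end of treatment. Its 6-month follow-up column therefore falls at about m = 6 or m = 9. Under either reading only the last column is free of pre-randomisation events.

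**The case against.** The strongest reply is that the article states no success rule. If all three domains had to succeed, type I error would not be inflated and the cost would fall on power. A success rule and the handling of multiplicity could also sit in an analysis plan that is not shown. This stands as a limit: the inflation is conditional on an any-one-wins reading. It does not remove the point. The article itself fixes three multi-measure primaries and one level for all inferences, and following it as written controls nothing across them.

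Three stronger readings are tempting, and the text does not support them.

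- A reader might multiply 14 measures by six visits and get 84 tests. Section 2.8 does not say every visit is tested, the decline items are not per-visit values, and exacerbations have no scheduled visit. For the same reason 51% does not apply to a single visit. It needs all 14 measures, each tested once.
- A reader might take the independent-test figures as the expected inflation. FVC and FVC%, or the several dyspnoea scales, are probably strongly correlated, so the true figure is lower, though still above 5% at an assumed correlation of 0.9.
- A reader might conclude that the exacerbation item cannot show a drug effect. Section 2.6.1.3 gives no assessment time, so the class may be meant as a baseline descriptor, and an assessment at 12 months or later would exclude earlier events. Pre-randomisation events should be balanced between arms on average, so they dilute a contrast but do not rule one out.

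**Conclusion.** The point holds in conditional form. Three domains with 14 numbered measures are declared primary, no variable or time point is chosen, and all inferences use two-sided 0.05. If any one significant result counts as success, the primary error rate is:

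- about 8–14% with one test per domain;
- about 12–37% for the 8–9 items measurable at one visit;
- about 14–51% for all 14 measures tested once each.

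The lower ends assume a correlation of 0.9 and the upper ends independence. The power figures of 65% and 79% under Bonferroni rest on assumed planning powers of 80% and 90%, since the article states none.

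It would go too far to say that the trial can give no controlled answer: a plan not shown could select one measure. This document does not.

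On exacerbations, the supported statement is narrow. The look-back is not tied to randomisation, it includes earlier events at any assessment before 12 months, and the item has no row in Table 2.

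**What to change.** Before unblinding, amend sections 2.6 and 2.8 and Table 2 as follows.

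- Name one primary variable and one time point, for example FEV1% predicted at the end of the 12-week treatment, tested at two-sided 0.05. This keeps the full level and needs no adjustment.
- Make the remaining spirometry, decline, CAT, mMRC, TDI, imaging and exacerbation measures secondary, tested in a fixed order or with Holm's adjustment, or report them descriptively.
- Take imaging and exacerbations out of the quality-of-life heading.
- Count exacerbations from randomisation and add a row for them to Table 2. Use the prior-12-month class only to describe patients at baseline.
- State which endpoint the 31 per group refers to, so that it can be matched to the chosen primary.

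The cost is a protocol amendment and fewer measures that can be claimed as primary. The choice of a single primary does not in itself call for more patients. Keeping three primaries with Bonferroni would: about 42 per group instead of 31 if 31 was sized for 80% power (assumed).

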##### 2.6.1.1 Lung function assessment​​

Pulmonary function testing (PFT) will be conducted under standardized protocols to ensure data validity and reproducibility. Patients will be instructed to abstain from inhaled bronchodilators for at least 24 h prior to testing to avoid transient airway dilation effects. Resting heart rate will be maintained below 120 bpm to minimize cardiovascular interference during spirometry. Key spirometric parameters included:① Forced Vital Capacity (FVC)​​: Measures the total volume of air exhaled forcefully after maximal inhalation. Reduced FVC indicates severe obstructive conditions.② FVC%​​: The ratio of measured FVC to predicted values (based on age, sex, and height). Values < 80% suggest significant impairment.③ FEV1%​​: The percentage of predicted forced expiratory volume in the first second, reflecting airflow limitation severity. Classified as mild (≥80%), moderate (50%–79%), or severe (<50%).④ FEV1/FVC Ratio​​: Critical for distinguishing obstructive (ratio <0.7) and restrictive (ratio ≥0.7 with reduced FVC) disorders.

##### 2.6.1.2 Long-term lung function decline

Long-term decline in lung function will be evaluated through serial spirometry conducted at baseline and predefined follow-up intervals (every 3 months). Patients with at least three valid pulmonary function tests over a 12- month period will be included in the analysis of decline trajectory. The following parameters will be used to quantify and classify lung function deterioration:① Annual FEV_1_ Decline (mL/year): The change in forced expiratory volume in 1 s (FEV_1_) over time will be calculated and expressed per year. A decline greater than 60 mL/year will be defined as “rapid decline,” in alignment with thresholds reported in GOLD and SPIROMICS cohorts. Declines between 30 and 60 mL/year will be considered moderate, while declines under 30 mL/year will reflect physiological aging.② Annual Change in FEV_1_% Predicted: The annual reduction in FEV_1_ as a percentage of predicted values will be computed. A reduction exceeding 5% per year will indicate clinically significant progression.③ FVC and FVC% Predicted Trends: Longitudinal changes in forced vital capacity (FVC) and its percentage of predicted will be monitored to detect potential restrictive patterns or lung volume loss.④ FEV_1_/FVC Ratio Decline: The ratio of FEV_1_ to FVC will be tracked over time. A progressive decrease in this ratio will reflect worsening airflow obstruction, particularly relevant in COPD progression.

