### 2.3 Participants

#### 2.3.1 Inclusion criteria

Patients who meet the following criteria will be included:1. Aged 40-75 years old;2. Meeting the Western medical diagnostic criteria and typing standards for active PTB;3. No use of steroids, anti-tuberculosis medications, or immunosuppressants, nor desensitization therapy administered within the past month;4. Documented comprehension of therapeutic protocols with voluntarily signed informed consent.

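### The primary long-term decline endpoint selects patients by tests completed after randomisation and annualises change from untreated tuberculosis, so an early treatment gain would be reported as slower decline

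*Protocol article*

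**What the plan says.** Section 2.6.1 gives the endpoint primary status: "Lung function, long-term lung function decline and quality of life were established as primary efficacy endpoints". Section 2.6.1.2 then fixes several features of it.

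- **Schedule:** "serial spirometry conducted at baseline and predefined follow-up intervals (every 3 months".
- **Analysis set:** "Patients with at least three valid pulmonary function tests over a 12- month period will be included in the analysis of decline trajectory".
- **Measure:** FEV1 change "over time will be calculated and expressed per year". No starting point other than baseline is named.
- **Classes:** for FEV1 in mL, "A decline greater than 60 mL/year will be defined as" rapid. A loss of 30 to 60 mL/year is moderate, and less than 30 is put down to normal ageing. For FEV1 as a percentage of predicted, "A reduction exceeding 5% per year will indicate clinically significant progression".

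Section 2.7 refers to a different grid: "Data collection will be carried out before, during, and after treatment (Table 2". Table 2 marks spirometry at baseline, at months 1, 2 and 3 of treatment, and at follow-up months 3, 6 and 12.

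The Introduction describes the patients as treatment-naive with active disease, and Section 2.3.1 requires "No use of steroids, anti-tuberculosis medications, or immunosuppressants, nor desensitization therapy administered within the past month". Section 2.5.2 has both arms receive anti-tuberculosis therapy and COPD maintenance treatment. Section 2.4 sizes the trial with intent-to-treat analysis in mind and expects 20% dropout.

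**The concern.** There are three problems, and each follows from what the article states.

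First, entry to the analysis depends on attending and producing valid tests after randomisation. Patients who leave early or cannot perform the manoeuvre are lost from a primary endpoint, and the arms may lose different kinds of patient.

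Second, the first test is taken in untreated active tuberculosis. Any recovery over the first months enters the same annual rate as later loss. The study pill is given for 12 weeks and is described in the Introduction as antiasthmatic and bronchodilating, so an early difference between arms is what the trial hopes to see. That difference would be read as slower long-term decline even if later decline were identical.

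Third, the mL/year classes are 30 mL/year wide, and one patient's slope over a year may be far less precise than that.

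**Working it through.** **The plan's own figure.** No effect, SD or power is stated for this endpoint. The only related figure is the total of 74, which follows from 62 × 1.2 = 74.4. At 20% dropout, 0.20 × 74 = 14.8, so about 15 patients could be lost.

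**Inputs.** Visit times come from Section 2.6.1.2 and Table 2. The within-patient SD of FEV1 (σ, 50 to 150 mL), the early gains, the rates of decline and the slope SD are assumptions, because the article gives none of them.

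**Formulas.** With t in years, slope b = Σ(t − t̄)y / Sxx, where Sxx = Σ(t − t̄)², and SE(b) = σ/√Sxx. The false arm difference is the slope fitted to an extra gain of 50 mL, reached linearly by month 3 and then kept, with identical decline in both arms.

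| Tests (months) | Sxx (yr²) | SE at σ = 50 / 100 / 150 mL (mL/yr) | False arm difference (mL/yr) |
|---|---|---|---|
| 0, 1, 2 | 0.0139 | 424 / 849 / 1273 | 200 |
| 0, 3, 6 | 0.125 | 141 / 283 / 424 | 100 |
| 0, 3, 6, 12 | 0.547 | 68 / 135 / 203 | 40 |
| 0, 3, 6, 9, 12 | 0.625 | 63 / 126 / 190 | 40 |
| 0, 1, 2, 3, 6, 12 | 0.681 | 61 / 121 / 182 | 41 |
| 3, 6, 12 | 0.292 | 93 / 185 / 278 | 0 |

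For 0, 3, 6, 12: t = 0, 0.25, 0.5, 1 and t̄ = 0.4375. The extra gain is 0, 50, 50, 50, so Σ(t − t̄)y = 50 × (−0.1875 + 0.0625 + 0.5625) = 21.875, and 21.875/0.547 = 40.

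**Selection.** On the three-monthly schedule the third test falls at month 6, so anyone who leaves before then is excluded. On the Table 2 grid the third test falls at month 2, and the first row of the table applies. To illustrate the bias, assume a between-patient slope SD of 60 mL/year and all losses from the worse half. The half-means then lie 60 × √(2/π) = 47.9 either side of the overall mean. Losing a fraction f shifts the retained mean by 47.9 × f/(1 − f): 5.3 at 10% and 12.0 at 20%. Losses of 20% against 10% bias the arm difference by about 7 mL/year, and 20% against none by about 12.

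**Recovery common to both arms.** Take a gain of 50 mL by month 3 and a true loss of 40 mL/year. Values at 0, 3, 6, 12 are 0, 40, 30, 10, and the fitted slope is (−7.5 + 1.875 + 5.625)/0.547 = 0. This drops out of the mean difference between arms tested at the same times. It does not drop out of the classes: a moderate decliner is moved to the lowest class.

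**Classes.** On 0, 3, 6, 9, 12 with σ = 100, SE = 126. A patient truly losing 20 mL/year is called rapid with probability 1 − Φ(40/126) = 38%. One truly losing 80 is called rapid with probability Φ(20/126) = 56%.

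**The case against.** The strongest reply is that both arms receive the same background treatment, so recovery common to both cancels in the randomised comparison. That stands for mean slopes on the same visits. A reader might infer that the endpoint cannot show whether decline slowed, but the documents do not support this: the planned later tests allow a slope from after treatment, and an unseen analysis plan may set the estimator. The fault is that the endpoint as written does not isolate decline.

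Section 2.6.1.1 requires 24 hours off inhaled bronchodilators before testing. This limits transient bronchodilator gain but does not remove recovery from tuberculosis.

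The two selection complaints depend on which tests count. If the monthly tests count, few patients are excluded and unusable slopes get in. If only the three-monthly tests count, the 0, 1, 2 case falls away and the exclusion matters more. The article does not settle this, and neither reading leaves the rule sound.

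Three further inferences do not hold.

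- **Contradictory cut-offs.** The 60 mL and 5% limits apply to different parameters under different labels. In mL they coincide only at a predicted FEV1 of 1.2 L (0.05 × 1,200 = 60), but nothing requires them to agree. What remains is that the article does not say whether 5% means percentage points or relative change.
- **A missing 9-month test.** If Table 2 follow-up is counted from the end of treatment, its visits fall at study months 6, 9 and 15, and a 9-month test exists. Only the time origin is unclear.
- **FEV1 in mL not collected.** It comes from the same manoeuvres as the listed measures, so this is only a matter of table labels.

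It is also fair that no passage makes an arm comparison of classes the primary test.

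**Conclusion.** The concern holds in this limited form. A primary endpoint is restricted by events after randomisation, against the article's own intent-to-treat aim, and its annual rate combines early recovery with later decline. With an assumed extra early gain of 50 mL in one arm and identical later decline, the false benefit is 40 mL/year on tests at 0, 3, 6 and 12 months and 0 from month 3 onward. It scales with the gain, so 25 mL would give 20 mL/year. The size of the selection bias is unknown; about 7 to 12 mL/year under the assumptions shown is only an illustration. The 30 mL/year bands are narrower than the error of one patient's one-year slope, about 61 to 190 mL/year for σ of 50 to 150 mL on the two fuller grids (0, 1, 2, 3, 6, 12 and 0, 3, 6, 9, 12). All these sizes rest on assumed inputs. The direction of the early-gain effect does not depend on them. Whether decline should be primary or secondary is a design preference and not part of this finding.

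**What to change.** 1. Remove the three-test condition. Analyse FEV1 in mL for all randomised patients with any post-baseline test in a linear mixed model with random intercept and slope, letting the mean slope change at month 3.
2. Report two contrasts separately: the arm difference in level at month 12, and the arm difference in slope after the treatment phase (month 3 onward). Base any statement about decline on the second.
3. Use the 30/60 mL and 5% classes for description only, and say whether 5% means points or relative change.
4. State the time origin of follow-up and reconcile the three-monthly schedule with Table 2. If follow-up is counted from the end of treatment, no test falls at month 12, and the level contrast needs a named visit. Table 2 also marks the study pill in the follow-up columns while Sections 2.1 and 2.5.1 give 12 weeks. These passages must be reconciled, because month 3 as the start of the later slope rests on the 12-week period.

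**Cost.** This is mainly wording in Section 2.6.1.2, Table 2 and the analysis plan, using data already scheduled. The price is precision. At σ = 100 mL, one patient's slope SE rises from 135 mL/year on 0, 3, 6, 12 to 185 on 3, 6, 12, a factor of 1.37. The mixed model also assumes that missing tests depend only on observed data, which calls for a sensitivity analysis.
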